### Confidentiality {27}

REDCap is 21 CRF Part 11 capable. Currently, REDCap installations support electronic signatures by positively identifying the user through a unique username and password combination. All study participants are allocated a unique number at time of screening (screening number or study ID number), and this screening number is added to all the CRFs for that participant. The participants also have their hospital record number (HRN) recorded on the CRFs as this information is required to ensure the correct medical record is accessed during medical record reviews.

Access to the REDCap database will be given to the study personnel only, including the biostatistician and data management personnel. Data being analysed will be exported in de-identified format. As part of the data dictionary development process, individual fields are denoted as “identifiers.” When exporting a de-identified dataset, these variables are omitted. Identities of participants will not be revealed in the presentation or publication of any result from this study. All study personnel are educated about the importance of strictly protecting participants’ rights to confidentiality and can only access the data necessary for job completion. Participants will be informed of law-mandated instances in which confidentially could be breached.

The trial management committee will be the custodians of the final trial dataset. No-one outside the trial management committee will be given access to the data without the permission of the trial management committee. No identifying data will be given to any third parties at any stage. Following study close out and locking of the database, it will be stored on the servers of the Menzies School of Health Research.

### Plans for collection, laboratory evaluation, and storage of biological specimens for genetic or molecular analysis in this trial/future use {33}

#### Laboratory procedures

All blood tests are processed as per the local laboratory’s usual procedures. Some samples will need to be processed by the Menzies laboratories and Western Diagnostics as per standard clinical practice. Please refer to the INFERR Laboratory Standard Operating Procedure (SOP) for further information (Additional file 3).

#### Storage and testing of biological specimens

To ensure availability of relevant samples for study procedures, the laboratory linked to each site will freeze and store some samples. These will later be transported for archiving in – 80 °C freezers at the Menzies School of Health Research laboratory and Territory Pathology laboratories at Darwin and Alice Springs. Samples are transported to Menzies in batches at four specified time points in the study—3 months after the recruitment of participant # 100, 200, 300, 400 and 576. Samples are identified by their INFERR study number and local laboratory specimen ID number.

No biological specimens will be collected in the study for genetic or molecular analysis.

## Statistical methods

### Statistical methods for primary and secondary outcomes {20a}

#### Statistical analysis plan

Data will be reported in accordance with the Consolidated Standards of Reporting Trials (CONSORT) guidelines for reporting of randomised trials. Demographic, clinical, biochemical and outcome data will be described by allocation arm. Continuous normally distributed data will be summarised with mean and standard deviations (SD), continuous not normally distributed variables with median and inter-quartile ranges (IQR). Categorical variables will be described with frequency and corresponding percentage.

#### Analysing primary and secondary outcomes

Primary and secondary endpoints will be analysed according to the intention-to-treat principles (All participants data will be analysed according to the treatment allocation, regardless of what treatment they received and either they completed the follow-up or not).

The dichotomous primary outcome and all the dichotomous secondary events will be analysed using time-to-first-event regression using Cox proportional hazard models where the duration of the follow-up will be censored at the first between: date of outcome of interest, end of study, date of withdrawal (including withdrawal due to change in renal replacement therapy modality) or lost to follow-up. Given that these are competing events, sensitivity analysis will include analysis using Fine and Gray regression models [49]. The effect of the intervention will be estimated as compared to placebo using hazard ratios with corresponding 95% confidence intervals and *p* values. Recurrent event outcomes (i.e. rates of hospitalisation) will be analysed using the method of Ghosh and Lin [50] or, as an alternative, using random effects log-binomial models or one of the extensions of the Cox proportional hazards model [51, 52]. The approach choice will be guided by the distribution of the time to event and results of goodness of fit statistics.

Continuous outcomes assessed at multiple time points (e.g. haemoglobin) will be analysed using linear mixed models with a fixed effect for study allocation arm and time point and a random intercept to model the correlation of measurement taken within the same individual.

All the models will be univariable and include treatment arm only as independent variable (linear mixed models will also include a variable for time each outcome repeat was recorded).

Sensitivity analyses using a multivariable model to adjust for potential confounders will be performed when these factors appear to be not equally distributed between the two allocation arms.

*Pre-defined secondary stratified analyses* will be performed, comparing the effect of treatment between allocation arms according to:
(i)The presence of active hepatitis B carriage (defined dichotomously by the presence of either measurable hepatitis B DNA according to PCR by the ABBOTT REALTIME HBV assay, or Hep B surface antigen positivity measured according to immunometric immunoassay (serum), at any time during the study).(ii)Average weekly haemodialysis attendance over the time included in the study, defined as an ordinal variable [in three groups: < 2.0 sessions/week, 2.0–2.75 sessions/week, > 2.75 sessions/week] for stratified analysis, as well as incorporated in Cox regression models with an interaction term between attendance group and treatment allocation group, as well as separately as an additional continuous variable in Cox proportional hazards regression modelling.(iii)Baseline ferritin threshold (≤ 1200 μg/L and > 1200 μg/L)(iv)According to presence/absence of comorbidities (diabetes, cardiovascular and cerebrovascular disease, lung disease).

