#### Secondary objectives

The secondary objectives are as follows: (1) to document serious adverse events – major cardiovascular events, rates of infections and all-cause hospitalisation rates associated with the intravenous iron therapy [2]. To assess the relationship between ferritin, total body iron levels, measures of iron status, inflammation and liver disease [3]. To determine the costs that associate with intravenous iron treatment in this setting.

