#### Secondary outcomes

Differences between the 2 treatment groups in change from baseline of haemoglobin (Hb) level at 3, 6, 12, 24, 30 and 36 months and over the follow-up period.The differences between the two study treatment arms assessed in a time-to-first-event analysis of the following, all are measured every 3 months after randomised unless otherwise stated:
A composite of non-fatal myocardial infarction, non-fatal stroke, hospitalisation for heart failure or death from any causeAll-cause deathHospitalisation with any new diagnosis of infectionsHospitalisation with a principal diagnosis of infectionVascular access thrombosisPeripheral vascular disease and/or amputationsAll-cause hospitalisationFatal and non-fatal cardiovascular event (myocardial infarctions (MI), stroke and hospitalisation for heart failure (HF))Fatal or non-fatal MIFatal or non-fatal strokeHeart failure hospitalisationLength of hospital stayESA resistive Index (ERI), defined as average weekly erythropoietin (EPO) dose per kg body weight (wt) per average haemoglobin (Hgb), over a 3-month period (ERI = (EPO/wt)/Hgb))Serious adverse events
All serious adverse eventsAll hospital admissionsInfections associated with hospitalisationAll-cause mortalityIron overload (measured by magnetic resonance imaging (MRI) FerriScan^@^ of the liver) measured within 6 months post randomisation and at between 12 and 24 months post randomisationCost analysis: an analysis of the financial costs of the treatment will be performed assessing the costs of ESA, iron, hospital admissions and procedures for the duration of follow-up among all patients assigned to intravenous iron compared to no iron treatment.

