### Sample size {14}

Maximal planned follow-up in the study will be 36 months (3 years). The 2-year rate of admission with first episode of infection or death in our patients on maintenance haemodialysis from 2000 to 2014 was 60%. In order to achieve a study power > 80% at 5% significance level in detecting a 30% reduction (from 60 to 48%) in the rate of first hospitalisation with all-cause infection or death, using the log-rank test (time-to-event modelling) assuming a 5% drop-out rate, 576 participants will be randomised 1:1 into each arm. The study also has > 90% power at 5% significance level of detecting a difference in haemoglobin of 5 g/L and standard deviation of 11.3 g/L based on published data [44, 45]. The sample size also provides enough power to determine differences within the ferritin strata.

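### The method for recurrent hospitalisation is to be chosen from the trial's own outcome data, among models that estimate different quantities

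*Protocol article*

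**What the plan says.** The protocol's section on analysing primary and secondary outcomes states: "Recurrent event outcomes (i.e. rates of hospitalisation) will be analysed using the method of Ghosh and Lin". As an alternative it permits "using random effects log-binomial models or one of the extensions of the Cox proportional hazards model". It then sets the selection rule: "The approach choice will be guided by the distribution of the time to event and results of goodness of fit statistics".

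It gives no threshold, no order among the alternatives, no named Cox extension and no statement that the choice is made blind to arm. It does not say whether the log-binomial model would have one record per patient or one per period. The same section says that all models contain treatment arm as the independent variable.

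Hospitalisation also appears in two other places. The secondary objectives, under serious adverse events, include "rates of infections and all-cause hospitalisation rates associated with the intravenous iron therapy". The list of secondary outcomes places all-cause hospitalisation under a different analysis: "The differences between the two study treatment arms assessed in a time-to-first-event analysis of the following, all are measured every 3 months".

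**The concern.** The distribution of the time to event and the fit statistics are known only once outcome data exist, so the analysis is settled after the data are in. This matters more than usual because the candidates are not rival estimators of one quantity:

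- Ghosh–Lin addresses the mean number of admissions, with death as a terminal event.
- A log-binomial model gives a risk ratio for a yes/no record.
- A Cox extension gives a hazard or intensity ratio, and its handling of death depends on which extension is used.

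Choosing the model therefore chooses the question. Goodness of fit cannot settle that choice, because the models are fitted to different outcomes with different likelihoods.

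At stake is a secondary outcome that also bears on the safety of intravenous iron. Death is common enough here to be part of the primary composite, so whether it counts as terminal or as ordinary censoring is not a detail.

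**Working it through.** **The plan's own figure.** The protocol states no figure for the recurrent-event analysis. Its only related figure is the primary sample size of 576. With 60% and 48% at 2 years, HR = ln(0.52)/ln(0.40) = 0.714. Events = 576 × 0.95 × 0.54 = 295. Schoenfeld's formula gives 82.6% power, in line with the stated value above 80%. This point does not touch that calculation.

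**Do the candidates estimate the same thing?** Take a true rate ratio of 0.75, from 2.0 to 1.5 admissions per year (assumed; Poisson, no deaths). The risk in a period of length T is 1 − exp(−rate × T).

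- 3-month records: (1 − e^−0.375)/(1 − e^−0.5) = 0.313/0.393 = 0.79.
- One record over 3 years: (1 − e^−4.5)/(1 − e^−6) = 0.989/0.998 = 0.99.

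The same effect is 0.75 as a rate ratio and 0.79 or 0.99 as a risk ratio, depending on a set-up the protocol does not state.

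**How many admissions does a binary record merge?** Share lost = 1 − (1 − P0)/(rate × T), where P0 is the probability of no admission in the period. P0 = exp(−rate × T) for Poisson counts, or 1/(1 + rate × T) with gamma frailty of variance 1. The protocol gives no admission rate, so a range is assumed. The value 0.458 is −ln(0.40)/2, the constant hazard implied by the 60% two-year figure. That figure is for first infection admission or death, so it serves only as a low anchor. Each cell runs from Poisson to gamma frailty.

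| Admissions per year (assumed) | 3-month records | Yearly records | One record over 3 years |
|---|---|---|---|
| 0.25 | 3.1–5.9% | 11.5–20.0% | 29.6–42.9% |
| 0.458 | 5.5–10.3% | 19.8–31.4% | 45.6–57.9% |
| 1 | 11.5–20.0% | 36.8–50.0% | 68.3–75.0% |
| 2 | 21.3–33.3% | 56.8–66.7% | 83.4–85.7% |
| 4 | 36.8–50.0% | 75.5–80.0% | 91.7–92.3% |

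With 3-month records, the grid on which outcomes are collected, the loss up to 2 per year is about 3–33%. With one record per patient over 3 years it is clearly above half from about 1 per year, and straddles half at 0.458.

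**What could choosing after the data cost in type I error?** Null simulation: 4,000 trials, 288 per arm, gamma frailty variance 1, follow-up 6 to 36 months, no deaths. Three analyses were run: robust event rate, 3-month repeated binary, and time to first event. Each alone rejected in 4.8–5.6% of trials. Taking the smallest p of the three gave 9.1% at 0.46 per year and 10.7% at 2 per year. Replacing the 3-month records by one yes/no per patient gave 10.5–12% at 1–2 per year. Taking the smaller p of only the rate and 3-month binary analyses gave 6.8–7.0% (3,000 trials).

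These are upper-bound illustrations. The plan's rule is fit, not smallest p. Time to first event is not among the recurrent-event options, and the two-analysis version omits the Cox extension that is.

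**The case against.** **The log-binomial model may be less damaging than it looks.** A reader might infer that it would discard most admissions and collapse power. The protocol specifies random effects, which implies several records per patient. Repeat admissions in different periods are then kept, and longer follow-up contributes more records. For a rate ratio of 0.75 with 576 patients, simulated power with 3-month records is 68% against 72% for a rate analysis at 1 admission per year, and 74% against 81% at 2 per year. A fall to about 30–36% appears only with one yes/no per patient. This objection stands against the stronger reading. It does not make a binary model a model for rates.

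**Ghosh–Lin is already named first, and a blinded choice is not excluded.** Both are true. But no condition is given for leaving the first method. Since the models contain treatment arm, fit statistics read literally come from models that include the treatment effect. The blinding section covers those assessing and analysing the primary outcomes and does not mention this choice.

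**Some Cox extensions do handle death.** Joint frailty models do, so it would be wrong to say that every extension treats death as ordinary censoring. The extension is not named, so its estimand is open.

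**The analysis plan may settle it.** Such detail is commonly left there. Here, however, the protocol states a rule rather than staying silent, and that rule depends on the data.

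**Log-binomial may be a slip for negative binomial.** That is possible, but the document does not show it.

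**Conclusion.** The point holds as a defect in a secondary analysis. The stated rule lets outcome data choose among different estimands by a criterion that cannot compare them, and one option does not model counts or rates.

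The size is bounded only loosely. The loss of admissions depends on an unstated record length and an assumed admission rate. A majority is lost only with long records, such as one per patient over 3 years at about 1 or more per year.

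A reader might take 9–12% as the actual type I error. The documents do not support that: it assumes the smallest p is picked from three analyses, one of them not on offer. Inflation is possible, but the stated rule gives no means of quantifying it.

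Nor is the primary result weakened. It is a time-to-first-event comparison with its own method and sample size.

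**What to change.** Before unblinding, in the analysis plan or a protocol amendment:

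1. Make Ghosh–Lin, with death as the terminal event, the single method for recurrent hospitalisation.
2. Delete the sentence that lets the time-to-event distribution and goodness of fit guide the choice.
3. Delete the log-binomial option.
4. If another recurrent-event model is wanted, name it as a sensitivity analysis, require that it use counts and follow-up time, and state how it handles death. A negative binomial model with log follow-up as offset would qualify, but it treats death as the end of follow-up, and the plan should say so.

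The cost is wording only. No patients, visits or data items change.

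### The haemoglobin mixed model has one common arm effect, so it cannot yield the six visit-specific differences that the outcome asks for, and it leaves out baseline haemoglobin

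*Protocol article*

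**What the plan says.** Under Secondary outcomes, the Protocol article defines the haemoglobin outcome as the difference between groups in "change from baseline of haemoglobin (Hb) level at 3, 6, 12, 24, 30 and 36 months and over the follow-up period". This asks for two things: six contrasts, one per named visit, and one overall contrast.

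Under Analysing primary and secondary outcomes, repeated continuous outcomes, with haemoglobin as the example, get "linear mixed models with a fixed effect for study allocation arm and time point and a random intercept". The list of terms is then closed: "All the models will be univariable and include treatment arm only as independent variable". The one exception is that "linear mixed models will also include a variable for time each outcome repeat was recorded". Multivariable adjustment is a sensitivity analysis that "will be performed when these factors appear to be not equally distributed between the two allocation arms".

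The text does not say whether the response is haemoglobin itself or its change from baseline, nor whether the baseline value is one of the modelled repeats. The Sample size section powers haemoglobin on a "difference in haemoglobin of 5 g/L and standard deviation of 11.3 g/L".

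**The concern.** An arm main effect with a time main effect forces the same treatment difference at every visit. A plan that asks for six visit-specific differences therefore has no model that gives them. Any modelled time course in the final report would have to come from a model that was not prespecified.

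A constant difference cannot be taken for granted in this design. Iron in the intervention arm can be withheld from month to month, both arms can receive rescue iron, and the doses of erythropoiesis-stimulating agents can be adjusted throughout. The contrast in iron exposure, and with it the haemoglobin difference, may change over time.

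Baseline haemoglobin is an eligibility measurement and is part of the monthly routine bloods, but it is not a stratification factor and not a planned covariate. Leaving it out of a randomised comparison does not bias the effect, but it discards precision that is free to obtain. Improved haemoglobin is named in the hypothesis that closes the article's background section, so the estimate deserves to be well specified even though it is secondary.

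**Working it through.** **Inputs.** From the Sample size section: difference 5 g/L, SD σ = 11.3 g/L, 576 participants randomised 1:1 (288 per arm), 5% drop-out (0.95 × 288 ≈ 274 per arm), 5% significance (taken as two-sided). From Secondary outcomes: six post-baseline visits, K = 6. The within-patient correlation ρ is not given and is assumed to lie between 0.3 and 0.7. Compound symmetry (which a random intercept implies), complete data and equal SD at all visits including baseline are also assumed.

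**1. The plan's own figure.** Two-means power is Φ(5/SE − 1.96) with SE = 11.3 × √(2/n).
- n = 288: SE = 0.942, power = 0.9996.
- n = 274: SE = 0.965, power = 0.9994.

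The stated power above 90% is reproduced. It is a single-time-point calculation and does not use the mixed model.

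**2. What the arm coefficient estimates.** With balanced data and a random intercept, the coefficient is the simple mean of the arm differences over the modelled visits.
- True differences 5, 5, 5, 5, 5, 5 give 30/6 = 5.0 g/L.
- True differences 1, 2, 4, 6, 8, 9 give 30/6 = 5.0 g/L.

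The two patterns cannot be told apart from this coefficient, so the six contrasts cannot be recovered.

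**3. Precision lost by omitting baseline.** In units of σ², the per-participant variance of the follow-up mean is:
- post-baseline values only: ρ + (1 − ρ)/K
- change score, unadjusted: ρ + (1 − ρ)/K + 1 − 2ρ
- baseline as covariate: ρ + (1 − ρ)/K − ρ²

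The standard error of the arm effect is √(2σ²v/274), where v is the variance above. For K = 6:

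| ρ (assumed) | post only: v, SE | change: v, SE | adjusted: v, SE | cut vs post only | cut vs change |
|---|---|---|---|---|---|
| 0.3 | 0.417, 0.62 | 0.817, 0.87 | 0.327, 0.55 | 22% | 60% |
| 0.5 | 0.583, 0.74 | 0.583, 0.74 | 0.333, 0.56 | 43% | 43% |
| 0.7 | 0.750, 0.84 | 0.350, 0.57 | 0.260, 0.49 | 65% | 26% |

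With K = 3, the cut against post-baseline values alone is 1 − 0.443/0.533 = 17% at ρ = 0.3 and 1 − 0.417/0.667 = 38% at ρ = 0.5.

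**4. Dilution, under one reading only.** If raw haemoglobin is the response and baseline is an outcome row, the zero difference at baseline enters the mean and the coefficient becomes K/(K + 1) of the true average. For a true 5 g/L this gives 5 × 3/4 = 3.75 (K = 3) or 5 × 6/7 = 4.29 (K = 6). With post-baseline rows only, or change scores, the average is unbiased.

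**5. Power under each variant.** With K = 6 and 274 per arm, power for 5 g/L stays above 99% in all cases. The lowest value is 0.9993, with baseline as an outcome row and ρ = 0.7.

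**The case against.** Several points on the other side are sound. Haemoglobin is secondary, the primary time-to-event analysis is untouched, and haemoglobin power is not at risk. Part of the outcome can be estimated: with post-baseline values or change scores as response, the arm coefficient is a valid average difference over follow-up. Descriptive summaries by arm are planned too, so unmodelled haemoglobin means over time are not ruled out.

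A reader might infer that the planned analysis understates the effect. The article does not support that. Dilution needs raw haemoglobin with a baseline outcome row, which is nowhere stated, and an outcome defined as change from baseline points more naturally to a change score.

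A reader might also call the random intercept wrong because it assumes equal correlation between near and distant visits. It is a standard choice, and the covariance structure is commonly left to an analysis plan. The precision figures in the working themselves assume that structure. If correlation decays with time, baseline predicts late visits less well and the gain there shrinks. The haemoglobin ceiling for eligibility (115 g/L) may also narrow the baseline spread and lower the correlation.

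Late visits will be thin. With uniform accrual over the stated recruitment dates and follow-up to 31 December 2023, both assumed, 41.0%, 21.2% and 1.6% of participants could reach months 24, 30 and 36. That is a separate matter. Confining the overall contrast to early visits, or demoting months 30 and 36, would redefine the outcome and not repair the model.

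The objection that model terms belong in a statistical analysis plan does not stand. The article fixes the terms itself and closes the list. Where it wants an interaction with treatment, as for dialysis attendance, it writes one.

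**Conclusion.** The mismatch between outcome and model is real and should be fixed. The model as specified gives one common arm coefficient and cannot produce the differences at 3, 6, 12, 24, 30 and 36 months. This follows from the text and needs no assumption.

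Omitting baseline haemoglobin is a loss of precision, not a bias. Its size rests on compound symmetry, complete data, equal variances and assumed correlations. It ranges from about a fifth to two fifths of the variance against post-baseline values alone (ρ 0.3 to 0.5), and from about three fifths down to a quarter against unadjusted change scores (ρ 0.3 to 0.7). Attenuation, for example from 5 to 4.3 g/L, is conditional on a reading that the article leaves open but does not state.

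The point does not threaten the primary analysis or the power for haemoglobin, so it is not a critical defect.

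**What to change.** Model post-baseline haemoglobin with fixed effects for arm, visit as a category, arm-by-visit and baseline haemoglobin. Baseline-by-visit and the randomisation strata (location and ferritin group) may be added. State that baseline haemoglobin is a covariate and not an outcome row. Report the arm difference at each of the six visits and their average over follow-up, as the outcome is already defined, and say how visits are weighted in that average. With baseline haemoglobin as a covariate, each arm difference in post-baseline haemoglobin is also the difference in change from baseline.

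The sentence that restricts all models to treatment arm, plus time for mixed models, needs a matching exception so that the two statements agree.

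The cost is a change of wording and a few model terms. No new data, visits or participants are needed. The change carries most weight if made before outcome data are examined by arm.

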## Assignments of interventions: allocations

### Sequence generation {16a}

Prior to proceeding with randomisation, the research nurse and/or investigator ensures informed consent has been obtained and documented and confirm that the participant is eligible to be enrolled. Participants are randomised using a module in the web-based study database, the Research Electronic Data Capture (REDCap) that is password protected and stored on a secure drive at Menzies School of Health Research. Compulsory fields required prior to randomisation are screening number (Study Identification number), confirmation of eligibility, age, hospital registration number (HRN), confirmation of consent, recruitment site (unit) and ferritin strata. Randomisation will be stratified by location (Top End and Central Australia) and ferritin strata (≤ 1200 μg/L and > 1200 μg/L) and will be in permuted blocks of variable block size. Participants are randomised in a 1:1 ratio to either Arm A: Intervention treatment group or Arm B: control group via REDCap, available 24 h per day, 7 days per week (Menzies School of Heath Research, Darwin).

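### Randomisation is stratified by location and baseline ferritin, but the main models leave both out, and covariates enter a sensitivity analysis only if they look unbalanced

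*Protocol article*

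**What the plan says.** Under Sequence generation {16a}: "Randomisation will be stratified by location (Top End and Central Australia) and ferritin strata". The ferritin cut is 1200 μg/L, which gives four strata. Allocation "will be in permuted blocks of variable block size", at 1:1.

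Under Analysing primary and secondary outcomes, the primary outcome is analysed by "time-to-first-event regression using Cox proportional hazard models". The same section then states: "All the models will be univariable and include treatment arm only as independent variable". The exception given there is that "linear mixed models will also include a variable for time each outcome repeat was recorded".

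Multivariable models are a sensitivity analysis. Those that "adjust for potential confounders will be performed when these factors appear to be not equally distributed between the two allocation arms".

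The pre-defined stratified analyses that follow include baseline ferritin at the same 1200 μg/L cut, and Cox models with terms for dialysis attendance. Location is not among them.

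**The concern.** A trial that balances allocation on two factors normally carries them into the analysis. Stratified blocks make the arms more alike on those factors than simple randomisation would. A standard error that ignores this is too large when the factors predict outcome, so precision is given away on the primary comparison. The Background section itself says that high ferritin is independently associated with hospitalisation and mortality, so one stratifier is presumed prognostic on the protocol's own account.

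The adjustment rule is a second weakness. In a randomised trial, imbalance arises by chance, and the benefit of adjustment comes from how strongly a covariate predicts outcome. A rule triggered by visible imbalance can bring in weak predictors and leave out strong ones. Because the blocks hold location and ferritin balanced, it would seldom select the two factors with the best claim to be in the model.

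**Working it through.** **Inputs from the Sample size section.** Two-year event rate 60% versus 48%, 5% significance (two-sided assumed), power above 80%, 5% drop-out, log-rank test, 576 participants (taken as the total, as in the Abstract).

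**The plan's own figure.**
- Hazard ratio under proportional hazards: ln(0.52)/ln(0.40) = 0.714.
- Comparing two proportions, 60% versus 48%, at 80% power: 270 per arm, 540 in total. 540/0.95 = 569, close to 576.
- Log-rank (Schoenfeld): events = 4(1.960 + 0.842)²/(ln 0.714)² = 276.
- Evaluable participants: 576 × 0.95 = 547. Expected events: 547 × 0.54 = 295. Power = Φ(√295/2 × 0.337 − 1.960) = 82.6%.

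The stated power above 80% therefore holds for an unadjusted log-rank test.

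**Effect of leaving the strata out.** The protocol gives no prognostic strength for either factor, so a range is assumed. The simulation used 547 participants, four equal strata, permuted blocks of 4 or 6 within strata, exponential times cut at two years, an overall control rate of 60% and a within-stratum hazard ratio of 0.714. There were 5,000 trials per setting. The Monte Carlo standard error is about 0.5 points for power and 0.3 points for type I error.

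| Assumed HR, location / ferritin | Power, arm only | Power, stratified | Type I error, arm only | Type I error, stratified |
|---|---|---|---|---|
| 1.0 / 1.0 | 82.5% | 82.5% | 4.8% | 5.0% |
| 1.3 / 1.3 | 82.9% | 83.4% | 4.8% | 5.1% |
| 1.5 / 1.5 | 81.4% | 83.5% | 4.3% | 4.9% |
| 2.0 / 1.5 | 78.7% | 82.0% | 4.2% | 4.9% |
| 2.0 / 2.0 | 77.3% | 82.1% | 3.9% | 5.0% |

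Repeat simulations with 576 participants and 24 months of follow-up gave gains of 0.3 to 1.0 points at 1.3/1.3, 1.0 to 1.8 at 1.5/1.5, 3.0 to 3.5 at 2.0/1.5, and 4.3 at 2.0/2.0. Direction and order of size agree throughout.

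**How to read the arm-only column.** The simulation fixes 0.714 within strata. With four equal strata of relative hazard g, and λ set so that the control mean of 1 − exp(−2λg) is 60%, the treated mean of 1 − exp(−2λ × 0.714 × g) is 48.7% at 2.0/1.5 and 49.0% at 2.0/2.0, not 48%. Part of the fall in arm-only power comes from this smaller overall difference. The gap between the two columns is the quantity of interest.

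**The trigger.** Stratified blocks keep the arms close on location and ferritin by design. A rule applied when factors look unequal will therefore rarely reach them.

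**The case against.** - **The primary analysis is fixed in advance.** A reader might infer that the data can choose the trial's main model. They cannot: the imbalance rule governs a sensitivity analysis only, and cannot alter the primary estimate or its p value. This stands.
- **The strata are not wholly ignored.** Ferritin at the randomisation cut is a pre-defined subgroup variable, and the attendance models carry extra terms. This stands as to scope, but a subgroup analysis does not adjust the primary comparison, and location is still absent.
- **Open-label conduct.** A reader might infer that open treatment lets the analyst steer the adjusted result. The blinding section says that those assessing and analysing the primary outcomes are blinded, and the trigger looks at covariates rather than outcomes. The inference is not supported.
- **Bias in the hazard ratio.** One simulation at 2.0/1.5 gave 0.726 unadjusted and 0.712 stratified. That is the expected gap between a marginal and a conditional hazard ratio. These are different quantities, so it does not show bias.
- **The SAP may settle it.** The list of confounders and the criterion for imbalance may well be left to a SAP. The arm-only models are different: the protocol states that choice, so it is not an omission.
- **The effect is small and assumed.** This is fair. At modest stratum effects the gain is about a point or less.

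**Conclusion.** The point holds as a matter of efficiency, not validity. The arm-only test does not inflate type I error. When the strata are prognostic it is conservative, at about 3.7% to 4.8% across the simulations. Stratifying gains about 1 point of power or less at assumed stratum hazard ratios of 1.3/1.3, 1 to 2 points at 1.5/1.5, and 3 to 5 points from 2.0/1.5 to 2.0/2.0. It loses nothing if the strata do not matter.

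The sizes rest on assumed stratum effects, equal strata, exponential times and full two-year follow-up. A reader might conclude from the last rows of the table that the trial is underpowered as planned. The documents do not support this: they give no stratum effects, and those rows also carry a smaller overall treatment difference than the plan's 60% versus 48%. Nor does this check address whether enough events will accrue on the trial's calendar, since every simulated participant had the full period.

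The imbalance trigger is a poor rule whatever the size of the stratum effects, but its reach is confined to the sensitivity analysis. The change is worth making because it is almost free.

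**What to change.** Before any outcome data by arm are seen, amend the analysis section or state in the SAP:

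1. The primary Cox model and log-rank test are stratified by location (Top End / Central Australia) and ferritin stratum (≤ 1200 / > 1200 μg/L).
2. Both factors enter the linear mixed models as covariates.
3. The adjusted sensitivity analysis uses prognostic covariates that the sponsor names in advance. The condition about unequal distribution is deleted.
4. The unadjusted estimate is reported as supportive.

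The cost is wording. Ferritin stratum and recruitment unit are compulsory fields at randomisation, and the First Nation Reference Groups section already assigns the units to the two regions. No new data and no change in sample size are needed. If the protocol sentence stays as it is, a SAP that adds the strata would contradict it, so the two should be changed together.
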